##### Active and Passive Range of Motion

The test consists of active and passive ankle joint ROM. The measurement will be in degrees using a handheld goniometer. Goniometry will be performed with the subject in a supine position with extended knees, and the measurement will be made at the neutral position between dorsal flexion and plantar flexion. The axis of the goniometer will be placed 2 cm below the medial malleolus, and its moving axis will be placed along the first metatarsal bone. The passive ROM will be determined as the range that the assessor is able to move the subject's ankle beginning in maximum plantarflexion to maximum dorsiflexion until any resistance is felt. Similarly, the active ROM will be measured by asking the participants to move joints maximally. The test will be performed at the baseline and post-intervention. Three measurements for the active and passive ROM will be taken, and the average will be calculated for the ankle dorsiflexion ROM.

##### Manual Muscle Testing for Ankle Dorsiflexors

In clinical practice, muscle strength is most often evaluated using the manual muscle strength testing of the Medical Research Council (MRC) grade. The ankle dorsiflexor strength will be graded according to the (MMT; graded from 0 (no contraction at all) to 5 (full range of movement against power and the same force as on the opposite side) for ankle dorsiflexor. The test will be performed at the baseline and post-intervention. To perform the test, the participant will be in short sitting with ankle plantarflexed. The assessor will be in front of the participant sitting using one hand to stabilize the leg just above the malleoli. The other hand will provide the resistance to the dorsal aspect of the foot. A participant will be asked to dorsiflex his/her ankle actively against the resistance (14).

##### 10-Meter Walk Test

The 10-MWT assesses self-selected preferred walking speed over a short duration with or without an assistive device. The participant will be asked to walk a total of 10 m where an acceleration zone is used for the participants to accelerate 2 m before entering the 6-m distance and 2 m to decelerate afterward. Speed is only calculated for the 6-m distance between the end zones. The 10-MWT is widely used in clinical practice and research for people with stroke and has been shown to have an excellent test–retest reliability (ICC > 0.95) (15). The minimal clinically important difference (MCID) is 0.14 m/s for substantial meaningful change (16). The test will be performed three times, and the resulting speeds obtained will be averaged and used for the analysis. The test will be performed at the baseline and post-intervention.

#### Secondary Outcome Measures Procedures

##### Timed Up and Go

The TUG assesses functional mobility by assessing an individual's ability to stand up, walk 3 m at a comfortable pace, turn 180**°**, walk back 3 m, and sit down (17). The TUG test has excellent reliability and validity in stroke population, and the minimal detectable change (MDC) is 2.9 s (18). **Two** practice trials of the TUG will be allowed to familiarize the participant with the task. TUG is a valid method for screening of functional mobility and risk for falls in community-dwelling elderly people (17).

##### Six-Minute Walk Test

It assesses the distance walked over 6 min as a test of aerobic capacity and endurance. In this test, the patient can have standing rest as many as they like, but the timer should keep recording. The number of rests taken, and the time will be documented. In addition, the patient can use any assistive device or braces and will be documented. Only minimum amount of assistance is accepted if the patient needs it, and the level of the assistance should be documented. The examiner should walk behind the patient at least half a step when the patient administering the test. Turnaround points are to be marked by a cone. The participants will be asked to eat a light meal and wear comfortable clothes and shoes. Participants will be informed every minute elapsed. The heart rate, blood pressure, and oxygen saturation will be taken before and after the test.

##### The Barthel Index

It contains 10 common ADL to assess disability (19). It includes feeding, grooming, bathing, dressing, bowel and bladder care, toilet use, ambulation, transfers, and stair climbing. The scale yields a total score out of 100. The higher the score, the greater the degree of functional independence. The MCID is 1.85 in stroke population (20). The BI has been demonstrated to be a useful instrument with high inter-rater reliability, internal consistency, convergent and predictive validity, and adequate responsiveness in stroke patients (21). The ADL performance of each patient will be rated primarily by interviewing the patients, their primary caregiver, or their nurse. Observation of performance will be applied if necessary. The BI has been translated into the Arabic language following the international guideline.

##### Medical Outcomes Survey (SF-36)

It is a health survey that evaluates QoL in clinical practice and research purposes. It has eight-dimensional subscales: physical functioning to assess physical activities limitation (e.g., lifting heavy objects, playing golf, climbing several flights of stairs, walking more than a mile, and bathing or dressing), role limitations due to physical health problems (e.g., difficulty performing the work or the daily activities), general health perceptions, vitality, social functioning (e.g., limitation in social activities due to physical or emotional problems), role limitations due to emotional problems (e.g., limitation in daily activities at work or other activities due to emotional problems), general mental health, and health transition. Answers will be in different scales with different anchor points. Total scores will range from 0 indicating the worst QoL to 100 indicating the best QoL. Thus, a higher score indicates a higher self-perceived QoL. SF-36 has been translated and validated into Arabic language (22, 23).

##### Rapid Assessment of Physical Activity

It is a 9-item, self-reported questionnaire that measures the levels of physical activity of adults older than 50 years. The response to each item is yes or no. The instructions for completing the questionnaire provide a brief description of three levels of physical activity (light, moderate, and vigorous) with graphic and text descriptions of the types of activities that fall into each category. The total score of the first seven items is from 1 to 7 points, with the score of a respondent categorized into one of five levels of physical activity: 1 = sedentary, 2 = underactive, 3 = regular underactive (light activities), 4 = regular underactive, and 5 = regular active. Responses to the strength training and flexibility items are scored separately, with strength training = 1, flexibility = 2, or both = 3 (24). The RAPA measure has been cross-culturally adapted and validated to the Arabic language (25).

##### Patient Health Questionnaire-9

It is an instrument to evaluate depression symptoms among different populations. It has nine items, and each item uses a Likert scale of four options to rate the depressive symptoms based on frequency and occurrence in the past 2 weeks such at:

0 not at all1 several days2 more than half the days3 nearly every day

A total score of 5–9 indicates minimal symptoms, 10–14 indicates moderate symptoms, 15–19 indicates major symptoms, and more than 20 indicates severe depression (26–28). Previous research reported it as a reliable and valid instrument for different populations including people with stroke (29). This instrument has been translated and validated into different languages including Arabic language (30, 31).

##### Fatigue Severity Scale

It is a self-reported questionnaire that consists of **nine** statements that rate the severity of the fatigue interference of the patient with certain activities. The items are scored from 1 to 7 with 1 = strongly disagree and 7 = strongly agree. The minimum score = 9 and the maximum score possible = 63. The higher score indicates greater fatigue severity (32). The mean score of the **nine** items will be used for statistical analysis. The FSS has been shown to have high internal consistency, good test–retest reliability, and good concurrent validity in several populations (33–35). The FSS scale has been translated and validated into the Arabic language (36).

##### Fall Efficacy Scale International

The Fall Efficacy Scale International has been used to assess the risk of fall in older adults and people with chronic conditions (37). It is a 16-item self-reported questionnaire. Each item involves an activity that scored by the participant using the 4-point Likert scale depending on how concerned to fall if they did this activity regardless of actual performance. The score ranges from 16 to 19 indicating low concern about fall, 20 to 27 indicating moderate concern, and 28 to 64 indicating a high risk of fall. This scale has been translated and validated into Arabic language (38).

### Procedure

#### Assignment of Intervention

##### Allocation Sequence Generation

The participants will be randomly allocated at a 1:1 ratio into either EG (*n* = 22) or NMES_sham_ (*n* = 22). The randomization process will be generated by an independent research assistant who is not involved in the treatment or data collection using an online randomization website (https://www.graphpad.com/quickcalcs/randomize1.cfm).

##### Allocation Concealment

All randomized allocations of participants will be placed in a sealed envelope for each participant with no further identification. A research assistant will prepare envelopes and withhold information from assessors and participants. After completing the baseline assessment, a research assistant will draw an envelope and inform a trained therapist who is not involved in the study about the allocation of patients.

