#### Intervention

After the informed consent, participants will complete an intake form for demographic data, past medical history, past surgical history, and activity level. Additionally, they will be screened for inclusion/exclusion criteria. Participants who meet the inclusion/exclusion criteria will be enrolled to the study and evaluated on the main outcomes prior to and after the intervention. The participants will be randomized using the above-mentioned method in allocation sequence generation and located in two groups.

All participants will receive a conventional rehabilitation program (CRP) including warming up, strengthening, stretching exercise, balance exercise, and gait training for 45 min/day, three times a week for 4 weeks (Table 1). In addition, EG will receive 30 min active NMES, and the placebo group will receive 30-min NMES_sham_. There is a variety in the duration of using the NMES in the literature from a few minutes to hours (39–41). However, 30 min of electrical stimulation is an acceptable time for the clinicians and patients in the clinical sitting, and to keep the adherence of the patient at the maximum level to the treatment program.

**Table 1 T1:** Description of conventional rehabilitation program components.

**Components**	**Time** **repetitions**	**Description**
Warming up	5 min	Bicycling using stationary bicycle or ergometer
Stretching exercise	5 min 3 × 10 s with 10-s rest	Unilateral for the following muscle groups: wrist flexors, biceps, pectoral major, shoulder extensors, quadriceps, hamstrings, gastrocnemius, and thigh adductors
Strengthening exercise	5 min 3 × 40 repetitions with 10-s rest 3 × 40 repetitions with 10-s rest	Upper extremity strengthening exercises using small pulley weight Lower extremity strengthening exercise using quadriceps chair
Postural control and balance	3 min 3 × 50 s with 10-s rest 3 min 3 × 50 s with 10-s rest 4 min 4 × 50 s with 10-s rest	Sit to stand transition with symmetrical weight bearing and trunk rotationDynamic balance activity includes low frequency sway and increase weight shifting on the affected side Gentle perturbations to displace COG using gymnastic ball or equilibrium
Upper extremity control	5 min 3 × 10 repetitions with 10-s rest	Moving the upper extremity with emphasis on scapular motion. For example, hand to mouth, hand to opposite side, and hand functions Grasping and releasing objective

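### As described, envelopes without identification are drawn after baseline, so a redraw or swap is neither prevented nor readily detected

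*Protocol article*

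**What the plan says.** Three sections of the protocol article bear on this.

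- **Allocation Sequence Generation:** "The randomization process will be generated by an independent research assistant who is not involved in the treatment or data collection", using an online tool, at 1:1 with 22 participants per arm.
- **Allocation Concealment:** "All randomized allocations of participants will be placed in a sealed envelope for each participant with no further identification". Next, "A research assistant will prepare envelopes and withhold information from assessors and participants". Then, once baseline measurements are complete, "a research assistant will draw an envelope and inform a trained therapist who is not involved in the study" about the allocation.
- **Intervention:** "The participants will be randomized using the above-mentioned method in allocation sequence generation and located in two groups".

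The Abstract reports that recruitment has started and is ongoing, so a change can still reach later participants.

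**The concern.** A generated list protects against selection at allocation when each participant's place on it is fixed before anyone learns the arm, and when departures from it leave a record. Here the article specifies two features that work against this: envelopes without further identification, and a draw. As described, no envelope belongs to a given participant or list position until it has been opened. If the opened allocation were unwelcome, the procedure contains no step that would stop a second draw or record that one took place.

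The timing matters. Allocating after baseline is good practice, but it means each participant's severity is already known at the site when the envelope is drawn. Under Statistical Analysis, the between-group test compares post-intervention values by independent t-test or Mann–Whitney test, and no baseline adjustment is stated for that test. An imbalance created at allocation would therefore pass into it. Blinding of the assessor and participants does not protect against this, because it acts after allocation.

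The same sentence has a smaller wording problem. It describes the therapist who is told the allocation as standing outside the study, yet Research Training says physical therapists were trained to deliver the intervention, and Data Management refers to the therapist who applies it.

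**Working it through.** The point is procedural, and the plan gives no figure to reproduce. The check is to follow one allocation through the text and then count what the described draw can and cannot reveal.

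**Following one allocation**

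1. *List.* An independent assistant generates it (Allocation Sequence Generation).
2. *List to envelope.* Allocations are sealed, one per participant, with no further identification (Allocation Concealment). No number linking an envelope to a list position is stated.
3. *Envelope to participant.* "After completing the baseline assessment, a research assistant will draw an envelope and inform a trained therapist" (Allocation Concealment). No opening order is stated, and nothing is written on the envelope before opening.
4. *People.* Only the generator of the list is called independent. Preparing and drawing are each given to a research assistant, without saying whether these are the same person or whether either generated the list.

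The link between list and participant is therefore missing at steps 2 and 3.

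**Counting (illustration only)**

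Inputs: 22 + 22 = 44 allocations (Allocation Sequence Generation). Assumptions: all 44 envelopes are prepared at the start, are indistinguishable, and are drawn at random.

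- *Agreement with the list.* At any position, P(match) = 0.5 × 0.5 + 0.5 × 0.5 = 0.5. Expected matches = 44 × 0.5 = 22 of 44.
- *Whole list reproduced.* The number of orderings is C(44,22) = 2,104,098,963,720, so the chance is 1 / 2,104,098,963,720 ≈ 4.8 × 10⁻¹³.
- *One redraw.* After the first envelope is opened, 43 remain, of which 22 hold the other arm. P(other arm) = 22/43 = 0.512, about 51%.
- *Final totals.* If the first envelope is kept for a later participant, the totals stay 22 and 22. If it is thrown away, the pool is one short and an end-of-trial count could show it.

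The first two results say that, on the literal reading, list order is not what governs assignment. They do not show bias, because a random draw from a mixed pool is itself random. The last two say that a single redraw would change the arm about half the time, and that the final balance cannot reveal a swap.

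**The case against.** The strongest reply is that the text can be read more kindly. The lack of further identification may mean only that the arm is not shown on the outside, which is itself a concealment measure. One envelope for each participant could imply assignment in advance, and to draw an envelope could mean simply to take it. The Intervention section says participants are randomised by the method already described. These readings are possible, and for that reason a reader who infers that the generated sequence is not followed goes further than the document allows. The word draw leans the other way, but it does not settle the matter.

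Second, even on the literal reading a blind draw from a mixed 22/22 pool is valid and ends balanced. This stands: the weakness is in traceability, not in randomness.

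Third, opacity, retention of envelopes and similar details are commonly left to a full protocol, which is not shown here. Their absence is not counted in this point. What remains is the method that the article does state.

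Fourth, real safeguards are described: an independent generator, sealed envelopes, allocation withheld from assessors and participants, and a draw only after enrolment and baseline. The therapist is told the result and is not said to hold or draw envelopes, so the point does not rest on an unblinded therapist choosing allocations. The remaining exposure is narrower: a redraw or swap at the moment of opening.

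A reader might also infer that tampering would leave no trace at all, or might put a figure on it as some number of steered participants per arm. Neither is supported. A broken seal or a final count could expose some irregularities, and the document offers no basis for any such number.

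**Conclusion.** The concern holds as a matter of traceability. As described, no envelope is tied to a list position or participant before opening, so a redraw or swap after baseline status is known is neither prevented nor readily detected. The resulting bias, if any, cannot be sized from the document, and nothing suggests that it has happened. The conclusion assumes that the Allocation Concealment section describes the actual practice. If envelopes are already numbered and opened in order, the defect is in the text alone. The stronger conclusions, that randomisation is invalid or that the list has been abandoned, do not follow.

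This is a cheap improvement worth making while recruitment continues. The therapist wording is a separate, minor inconsistency with Research Training and Data Management.

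**What to change.** For participants not yet randomised:

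- Number the sealed envelopes sequentially. If earlier envelopes were drawn out of list order, the arms left in the pool need not match the rest of the list, so renumbering alone cannot restore it. In that case the independent assistant who generated the list should re-shuffle the remaining allocations or generate a new order for them.
- Open envelopes strictly in number order after the baseline assessment, with participant ID and date written on each before it is opened.
- Keep a log and reconcile it to the list.
- State that the person who opens the envelopes did not generate the list.
- Reword the description of the informed therapist to say not involved in outcome assessment.

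Participants already randomised keep their allocations, and the procedure used for them is documented. If numbering and ordered opening are already in place, correcting the text is enough.

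The cost is a log sheet and a little paperwork. The separation of roles can use the assistants already in place if there is more than one, which the article does not make clear; if there is only one, someone else must be named to open the envelopes. Sample size, treatment and analysis are unaffected.

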##### Blinding

In this double-blind study, the assessor and participants will be blinded to the allocation of group. The assessor will be banned from attending interventional sessions for both groups, and the allocation of participants will be managed in schedules to minimize contact between participants in both groups.

#### Intervention

After the informed consent, participants will complete an intake form for demographic data, past medical history, past surgical history, and activity level. Additionally, they will be screened for inclusion/exclusion criteria. Participants who meet the inclusion/exclusion criteria will be enrolled to the study and evaluated on the main outcomes prior to and after the intervention. The participants will be randomized using the above-mentioned method in allocation sequence generation and located in two groups.

All participants will receive a conventional rehabilitation program (CRP) including warming up, strengthening, stretching exercise, balance exercise, and gait training for 45 min/day, three times a week for 4 weeks (Table 1). In addition, EG will receive 30 min active NMES, and the placebo group will receive 30-min NMES_sham_. There is a variety in the duration of using the NMES in the literature from a few minutes to hours (39–41). However, 30 min of electrical stimulation is an acceptable time for the clinicians and patients in the clinical sitting, and to keep the adherence of the patient at the maximum level to the treatment program.

**Table 1 T1:** Description of conventional rehabilitation program components.

**Components**	**Time** **repetitions**	**Description**
Warming up	5 min	Bicycling using stationary bicycle or ergometer
Stretching exercise	5 min 3 × 10 s with 10-s rest	Unilateral for the following muscle groups: wrist flexors, biceps, pectoral major, shoulder extensors, quadriceps, hamstrings, gastrocnemius, and thigh adductors
Strengthening exercise	5 min 3 × 40 repetitions with 10-s rest 3 × 40 repetitions with 10-s rest	Upper extremity strengthening exercises using small pulley weight Lower extremity strengthening exercise using quadriceps chair
Postural control and balance	3 min 3 × 50 s with 10-s rest 3 min 3 × 50 s with 10-s rest 4 min 4 × 50 s with 10-s rest	Sit to stand transition with symmetrical weight bearing and trunk rotationDynamic balance activity includes low frequency sway and increase weight shifting on the affected side Gentle perturbations to displace COG using gymnastic ball or equilibrium
Upper extremity control	5 min 3 × 10 repetitions with 10-s rest	Moving the upper extremity with emphasis on scapular motion. For example, hand to mouth, hand to opposite side, and hand functions Grasping and releasing objective
Lower extremity control	3 min 3 × 10 s with 10-s rest	Pre-gait mat activity includes hook lying, bridging, and lower trunk rotation
Gait training	12 min 12 × 30 s with 30-s rest	Gait training using parallel bar. Gait training includes forward, backward, sideward step, and in crossed pattern

The equipment Gymna ([name]) will be used for active and placebo Russian electrical stimulation therapy. A frequency up to 100 Hz is acceptable for treatment and produces muscle contraction in a clinical setting. Low frequency produces low muscle contraction (twitches or a tremor). As the frequency increases, the muscle contraction increases and, therefore; muscle strength increases (42). However, we will select 80 Hz to stimulate dorsiflexor muscle strength without getting the risk of getting the maximum high frequency. Table 2 shows the parameters that will be used in the active electrical stimulation.

**Table 2 T2:** Parameters for active electrical stimulation.

Carrier wave	2.5 kHz
Burst	80 Hz
On time	5 s
Off time	15 s
Treatment time	30 min
Current type	Constant current
Waveform	Sinusoidal

The NMES delivered the electrical current through two surface electrodes (6 × 8 cm) inserted in saline-soaked sponges. The intensity of stimulation will be set within the tolerance level of the subject. The amplitude will be adjusted to produce visible ankle dorsiflexor muscle contraction without affecting the comfort of the patient. The cathode electrode will be placed over the common peroneal nerve as it passes over the head of the fibula, and the anode will be placed on the middle of the ankle dorsiflexor muscle belly on one-third of the line between the fibular head and the medial malleolus on the paretic limb (see Figure 2).

